#### Cognitive distortions

Cognitive distortions will be measured at baseline with de How I Think Questionnaire (HIT-Q), a 54-item 6-point Likert-type self-report questionnaire [106–108]. Of these items, 39 can be clustered into four categories of self-serving cognitive distortions: 1) self-centeredness, 2) blaming others, 3) minimizing/mislabeling, and 4) assuming the worst. All beforementioned 39 items are matched to one of the four antisocial behavioral categories of the DSM-IV-TR: 1) opposition-defiance, 2) physical aggression, 3) lying, and 4) stealing. Furthermore, other items consist of anomalous-responding items (8 items) and positive fillers (7 items). The HIT-Q demonstrated good psychometric properties in terms of reliability as well as convergent and divergent validity [109, 110].

#### Program integrity

In order to assess whether the intervention is implemented as intended and in accordance with protocols, program integrity is measured with a self-developed questionnaire. The instrument consists of questions about general characteristics of coaches, program evaluation and an estimation of patients’ adherence or motivation. Researchers will fill out the questionnaires together with coaches at the end of the intervention (12 months after baseline).

### Other variables of interest

A qualitative interview of experiences will be obtained with self-developed topic lists [111] to evaluate experiences of both participants and network coaches during coaching.

### Ethical and safety reporting

All Adverse Events (AE; e.g. undesirable events that occur to a subject during the study) and Serious Adverse Events (SAE; e.g. life-threatening medical events resulting in significant disabilities, hospitalisation or death) will be documented by the researchers. The principle investigator and ethics committee will be informed when a SAE occurs.

### Data management

After inclusion, a unique project number will be allocated to each participant. The key of these project numbers will be stored in a password protected file. All paper and digital data will be stored encoded in an online validated data management environment - Castor EDC - by a research assistant. All stored data will be double checked, corrected (if necessary) and signed. Only principal investigators and trained research associates will have access to Castor EDC and research files. Paper questionnaires, other data and informed consents will be stored in a locked cabinet at the participating site. Data will be stored for 15 years according to legislation. Storage of data will be supervised by the principal investigator in compliance with the Dutch Personal Data Protection Act.

The study will be conducted based on the quality handbook of the Amsterdam Public Health (APH) research institute. Data monitoring is provided by independent researchers at the Arkin Institute for Mental Health. An audit can be initiated by an independent researcher of the Amsterdam University Medical Centre throughout the course of the study. During an audit the independent researcher will investigate whether the execution of the study is based on the quality standards of the APH research institute.

## Statistical analysis

An intention-to-treat analysis will be included in the data analyses of the primary outcome measure (mental wellbeing) and secondary outcome measures (psychiatric functioning, criminal recidivism, substance abuse, quality of life, social network, social support, loneliness and self-sufficiency). Besides, subgroup analyses will be conducted on the protocol completers sample. Generalized Linear Mixed Models (GLMM) in Statistical Package for the Social Sciences (SPSS) will be used to model all continuous outcome measures, considering the distributional characteristics of the data. If the normal distribution assumption is violated, resampling methods will be used to transform data into a normal distribution or appropriate non-parametric tests will be used. Generalized Estimating Equations (GEE) will be used to analyze the categorical outcome measures. The main between-group effect (TAU versus FNC) and the interaction effect (group * time) will be analyzed whilst correcting for baseline assessment. Outcome data of all assessments will be included in the analyses to examine the differences in the development in time between both groups. The criminal recidivism data will be analyzed using Survival Analysis and corrected for time at risk. Missing data will be addressed using multiple imputation or statistical techniques that control for missingness-at-random.

To assess the magnitude of treatment effects on the primary outcome and secondary outcomes, Cohen’s *f* effect size will be calculated. Effect sizes of *f* = 0.40 are considered large, effect sizes of *f* = 0.25 are considered moderate and effect sizes of *f* = 0.10 are considered small (Cohen, 1988).

Moderator analyses will be used to examine potential moderators of treatment outcome by adding potential moderators as covariates of factors to the GLMM/GEE analyses. Furthermore, multilevel mediation models will be carried out to examine potential mediators of treatment outcome. At last, appropriate statistical methodology in ATLAS.ti will be used for the analyses of the qualitative data [111].

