### Research aims

The first aim of this study is to examine the effectiveness of the addition of FNC to treatment as usual (TAU) on the mental wellbeing among forensic psychiatric outpatients with social network problems and limited social participation. We expect significantly enhanced mental wellbeing rates in FNC as compared to TAU alone, by improving social networks, social support and social participation. The second aim is to examine the effectiveness of the addition of FNC on psychiatric functioning, criminal recidivism, addiction and other secondary outcomes (quality of life, social network, social support, loneliness, self-sufficiency). We expect significant improvements on psychiatric functioning, criminal recidivism and addiction, as well as on other secondary outcomes, in the FNC condition as compared to TAU. The third aim of this study is to gain insight into the development of the primary and secondary outcomes over time. To enhance knowledge regarding the underlying mechanisms, a variety of potential mediators and moderators will be explored.

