#### Randomization and procedure

Independent research assistants and research associates - not familiar with the patient or responsible for any kind of mental health care - of the research department of Inforsa are involved in the recruitment procedure, randomization, data collection and data management of this study. Randomization will be performed at an individual level, stratified by forensic outpatient care site. We aim to carry out randomisation after completion of (the first half of) the baseline assessment. A computer-generated block randomization schedule provided by Castor Electronic Data Capture (EDC) is used. The allocation ratio will be 1:1 to ensure that an equal number of patients will be allocated to either TAU or FNC. Researchers will not have access to the randomization schedule and will be blind to block size and order. Blinding for treatment after randomization is not possible, as the content of treatment will be clear to both patients and therapists. Blinding researchers is not feasible due to different assessments of the conditions and required coordinating activities - referring patients to FNC and monitoring - of researchers during the FNC intervention.

The experimental intervention starts preferably within 2 months after completion of the baseline assessment and ends 12 months after baseline assessment. During the intervention, patients in both FNC and TAU condition will be assessed at 3, 6 and 9 months after baseline assessment. At the end of treatment (12 months) and follow-up (18 months) additional questionnaires will be administered. Figure 1 provides an overview of the trial design. Two supplemental measures, the Work Alliance Questionnaire (WAV-12) and a qualitative interview, will only be assessed in the experimental group. Table 1 provides an overview of all instruments and the corresponding time of assessment.

**Table 1 Tab1:** Overview of outcome measures, instruments and time of assessment from baseline in months

Outcome	Concept	Instrument	baseline 0	3	6	9	end 12	follow-up 18	36
**Primary**	Mental wellbeing	MHC-SF	•	•	•	•	•	•	
**Secondary**	Psychiatric functioning^a^	HoNOS	•	•	•	•	•	•	
	Criminal recidivism	SRD	•				•	•	
		IPOL					•		•
		JDS					•		•
	Substance abuse	MATE 2.1	•	•	•	•	•	•	
	Quality of life	MANSA	•	•	•	•	•	•	
	Social network	NGI-method	•				•	•	
	Social support	SSL	•				•	•	
	Loneliness	Loneliness Scale	•				•	•	
	Self-sufficiency	SSM-D	•	•	•	•	•	•	

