#### Social network

The size and quality of the social support network is measured with a self-developed interview based on the Modified Multiple Generator (MMG) [83] and Name Generator/Interpreter method (NGI) [84]. The NGI method is widely used in sociological research to investigate the size and quality of different type of social networks and changes in social networks [83, 85]. The MMG approach is a time-saving alternative of the NGI method, and therefore more appropriate for the current study. Two widely used name generator questions (“who are the people with whom you discuss matters important to you” and “who are the people you really enjoy socializing with”) are administered to determine the size of the social support network. If participants report more than five names, they will be asked to mention the five most important network members. Additionally, name interpreter questions are administered to measure the demographic characteristics of network members, the quality of the relationships and contact frequencies. Even though content validity of the MMG approach is less strong, when compared with the full NGI method, the MMG is found to be an acceptable alternative [83]. The instrument will be administered at baseline and 12 and 18 months after baseline.

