#### Self-sufficiency

Self-sufficiency will be measured with the Dutch version of the Self-Sufficiency Matrix (SSM-D) at baseline, and 3, 6, 9, 12 and 18 months after baseline assessment. The SSM-D is a 13-item 5-point Likert-type assessment tool of treatment outcomes [44, 45, 91, 92]. Self-sufficiency on 11 important domains of life, such as physical health, mental health, addiction, income, housing, social network, social participation and justice, are measured. The SSM-D is validated for the Dutch population [91] and demonstrated adequate psychometric properties [93, 94].

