The present study has several strengths. First, to our knowledge, this is the first RCT that examines the effectiveness of a social network intervention within a forensic outpatient population. The field of forensic (outpatient) care is in urgent need of more RCTs in order to gain knowledge about evidence-based practice [23, 24]. Therefore, this study will contribute to the existing knowledge about effective forensic interventions. Secondly, this RCT is embedded in clinical day-to-day practice resulting in high ecological study validity. Hence, it is possible to account for the specific needs of patients, professionals, managers and policy makers. Thirdly, the research group has chosen to include a wide range of primary and secondary outcome variables. Multiple participant and intervention characteristics will be examined to provide insight regarding potential mediators and moderators of treatment effectiveness. Besides, many different types of instruments (i.e. electronic patient files, self-report instruments, reports from coaches and registrations from trained researchers and information sources) will be used to gather this information. Information about program integrity and dosage will be studied as a potential moderator of intervention effects. Moreover, qualitative and quantitative methods will be combined to study intervention effects. Lastly, the large amount of clinically relevant outcome measures will be administered during a long follow-up period of 18 months with multiple assessment points. Therefore, it will be possible to gather valuable information about changes in important life areas over a longer period of time.

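### As written, the moderator analysis does not test moderation: no group-by-moderator term is named, and variables that exist or vary only in the FNC arm are planned as moderators of the intervention effect

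*Protocol article*

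**What the plan says.** All references are to the protocol article.

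- **Moderators.** The Statistical analysis section examines them "by adding potential moderators as covariates of factors to the GLMM/GEE analyses" (the word *of* is probably a slip for *or*). The one interaction named in that section is group by time.
- **Integrity and dosage.** The Discussion lists among the strengths that "Information about program integrity and dosage will be studied as a potential moderator of intervention effects". A footnote to Table 1 restricts program integrity to coaches in the experimental group, and the Program integrity section places it at 12 months.
- **Working alliance.** It stands in the Mediators / Moderators block of Table 1, but under Randomization and procedure: "Two supplemental measures, the Work Alliance Questionnaire (WAV-12) and a qualitative interview, will only be assessed in the experimental group".
- **Mediators.** The Statistical analysis section says that "multilevel mediation models will be carried out to examine potential mediators of treatment outcome" and names neither the mediators nor a lag. Research aims gives the expected route to better wellbeing, "by improving social networks, social support and social participation", and describes the work as exploratory: "a variety of potential mediators and moderators will be explored".
- **Timing.** Of the network interview: "The instrument will be administered at baseline and 12 and 18 months after baseline". The SSL has the same schedule. In contrast, self-sufficiency is measured with the "Self-Sufficiency Matrix (SSM-D) at baseline, and 3, 6, 9, 12 and 18 months after baseline assessment", and its domains include social network and social participation. The main outcome is MHC-SF change from baseline to 12 months; MHC-SF is also taken at 3, 6, 9 and 18 months.

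**The concern.** A variable moderates the effect of FNC if the FNC-minus-TAU difference varies with it. That is an interaction with group. A covariate or factor entered as a main effect answers a different question: whether patients with different values have different outcomes, whichever arm they are in. An analyst who follows the stated method would report prognostic variables as moderators and could miss true ones.

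For variables that exist only under FNC the problem is not wording alone. There is no TAU value to compare with, so what comes out is an association within one arm between something that arose after randomisation and the outcome. Motivated or less impaired patients may both form better alliances and do better, and randomisation does not protect against that.

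The mediation part is a lesser matter. If the network interview and the SSL are related to wellbeing at the visit where both are taken, the direction of influence is open. The article presents insight into mediators and moderators as one of the trial's contributions, so the labels on these results matter even though the work is exploratory.

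**Working it through.** The article states no figure on this point. The check sets schedule, arm coverage and model side by side, then adds three illustrations. Their effect sizes are assumptions, not figures from the article.

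**1. Which variables can carry a group interaction**

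| Variable | Arms | When | Interaction with group estimable? |
|---|---|---|---|
| Diagnoses, CTQ-SF, SCIL, HIT-Q | both | baseline | yes |
| ASQ | both | 0, 12 months | yes, using the baseline value |
| Demographics | both | 0, 12, 18 months | yes, using the baseline value |
| Working alliance | FNC only | 3, 6, 9, 12 months | no |
| Program integrity | FNC only | 12 months | no |
| Coaching dosage | nil in TAU by design | during FNC | no |

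Let G = 1 for FNC and 0 for TAU. If a variable V is set to 0 throughout TAU, then G×V = V for every patient. The two columns are identical, and the one coefficient that can be fitted is the slope of outcome on V within FNC. If V is left missing in TAU, those patients drop out and the same slope remains.

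**2. Covariate versus interaction**

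Assume a 50/50 binary moderator M independent of group, and outcome = 0.8·G·M − 0.4·M + noise (SD 1). The effect of FNC is 0.8 when M = 1 and 0 when M = 0.

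- Covariate-only model: the coefficient of M is the average of its effect in the two arms, 0.5 × (−0.4) + 0.5 × (0.8 − 0.4) = 0. Simulation: 0.00.
- Model with G×M: expected 0.8. Simulation: 0.80.

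The covariate model sees nothing although the effect differs completely between the halves.

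**3. Same-visit mediation**

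Assume FNC raises wellbeing by 0.4 SD, wellbeing drives the mediator (slope 0.5, mediator residual variance 0.75), and the mediator has no effect on wellbeing.

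- Group to mediator: a = 0.5 × 0.4 = 0.20.
- Mediator to wellbeing, given group: b = 0.5 / (0.25 + 0.75) = 0.50.
- Apparent indirect effect: a × b = 0.10 SD, or 0.10 / 0.40 = 25% of the effect (simulation: about 24%).

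The true mediated share is zero. Same-visit data cannot tell the two directions apart.

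**4. What a correct interaction test could detect**

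The plan's 105 patients and 30% drop-out give 105 × 0.7 = 73.5, taken as 73. Assume a 50/50 moderator, four equal cells, a 12-month comparison adjusted for baseline, and the plan's correlation of 0.50.

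- Residual SD = √(1 − 0.25) = 0.866.
- SE of the difference in effects = 0.866 × √(16/73) = 0.405.
- Detectable with 80% power: (1.960 + 0.842) × 0.405 = 1.14 SD.
- Power for a difference of 0.4 SD: 1 − Φ(1.960 − 0.4/0.405) ≈ 17%.

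Even the right test is therefore only exploratory at this size.

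**5. Time order available in the schedule**

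The network interview and SSL have no value between months 0 and 12. The SSM-D social network and social participation domains have values at 3, 6 and 9 months, and patients in both arms are assessed at those visits. MHC-SF at 18 months follows the 12-month network interview and SSL.

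**The case against.** The strongest defence is that the moderator sentence is shorthand. It appears under moderator analyses and adds variables to a model that already holds group and group by time; covariates and factors are the software's terms for types of predictor. It does not exclude interactions, and a condensed article may leave the term to the full protocol. This is fair as to intent. What stands is that a method is stated, and taken at its word it does not test moderation.

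The integrity and dosage label is in the Discussion, while the Statistical analysis section speaks of moderators of treatment outcome, which could cover within-arm work. That softens the point but leaves the Discussion's claim about intervention effects unsupported. No analysis plan can supply the missing TAU values.

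On mediation, a reader might infer that the hypothesised mediators are all first re-measured with the primary outcome, so that the mechanism aim cannot be answered. The article does not support that. SSM-D covers two of the three expected routes every three months; MANSA, on the same schedule, touches on social relationships; and MHC-SF continues to 18 months. Nor does the article commit to same-visit models; it simply names no lag, which a condensed article may leave open. The timing limit applies to the network interview and the SSL. It applies also to the Loneliness Scale, but loneliness is not one of the routes named in Research aims.

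**Conclusion.** The point holds in two parts, with a secondary remark.

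1. The stated moderator model, followed literally, tests prognosis rather than moderation. The size of the error depends on the data; the illustration shows that it can hide a complete difference in effect (0.00 against 0.80).
2. Working alliance, program integrity and dosage cannot moderate or mediate the FNC-versus-TAU contrast. This follows from arm coverage alone and needs no assumption about effect sizes.
3. For the 12-month outcome, the network interview and SSL can give only same-visit associations. This limits two instruments at one endpoint; it does not make the mechanism aim unanswerable.

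The work is exploratory and no primary or secondary comparison of the arms depends on it, so this is a correction that should be made rather than a threat to the trial's main result. The power figures rest on a balanced moderator and 73 completers; an unbalanced moderator would do worse.

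**What to change.** - **Moderators.** State that moderation is tested by a group-by-moderator (by-time) term, with the contrast taken at 12 months, for baseline variables measured in both arms. Report estimates with confidence intervals and say that power is low.
- **FNC-only variables.** Describe working alliance, program integrity and dosage as predictors of outcome within FNC, not protected by randomisation, and change the Discussion sentence to match.
- **Mediators.** Name them and fix the order: SSM-D social network and social participation items at 3 to 9 months for MHC-SF at 12 months; network interview and SSL at 12 months for MHC-SF at 18 months, adjusted for earlier MHC-SF. Label any same-visit model as associational.

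The cost is analysis wording, with no new visits or instruments. There are two drawbacks. SSM-D items are coarser than the network interview or the SSL, and the 18-month models speak to later wellbeing rather than to the primary 12-month contrast. Time order also does not remove confounding between mediator and outcome, so the results remain exploratory.

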## Discussion

This article describes the study protocol of a randomized controlled trial to examine the effectiveness of the addition of an informal social network intervention (FNC) to TAU in a forensic psychiatric outpatient population. Considering the severe and multiple problems that are observed in forensic populations, more knowledge about multimodal evidence-based interventions is warranted. Social network-related problems of forensic psychiatric patients are considered one of the important targets in forensic treatment. Previous research indicates that the absence of a supportive social network can increase the risk of criminal recidivism, whereas a supportive social network can decrease the risk of criminal recidivism. Despite this, evidence-based interventions aimed at improving social networks of forensic outpatients are not available. Therefore, this RCT examines the effectiveness of the addition of FNC to TAU in improving mental wellbeing, psychiatric functioning and decreasing criminal recidivism of forensic psychiatric outpatients. We will also examine the effectiveness of the addition of FNC to TAU on several secondary outcome measures. Furthermore, this study will explore the development of a broad range of primary and secondary outcomes over time and the impact of relevant patient- and intervention-related characteristics. If effectiveness is shown, the social network intervention - based on a collaboration between formal and informal care - can be implemented more extensively within the field of forensic mental health care.

The present study has several strengths. First, to our knowledge, this is the first RCT that examines the effectiveness of a social network intervention within a forensic outpatient population. The field of forensic (outpatient) care is in urgent need of more RCTs in order to gain knowledge about evidence-based practice [23, 24]. Therefore, this study will contribute to the existing knowledge about effective forensic interventions. Secondly, this RCT is embedded in clinical day-to-day practice resulting in high ecological study validity. Hence, it is possible to account for the specific needs of patients, professionals, managers and policy makers. Thirdly, the research group has chosen to include a wide range of primary and secondary outcome variables. Multiple participant and intervention characteristics will be examined to provide insight regarding potential mediators and moderators of treatment effectiveness. Besides, many different types of instruments (i.e. electronic patient files, self-report instruments, reports from coaches and registrations from trained researchers and information sources) will be used to gather this information. Information about program integrity and dosage will be studied as a potential moderator of intervention effects. Moreover, qualitative and quantitative methods will be combined to study intervention effects. Lastly, the large amount of clinically relevant outcome measures will be administered during a long follow-up period of 18 months with multiple assessment points. Therefore, it will be possible to gather valuable information about changes in important life areas over a longer period of time.

Given the beforementioned strengths, several pragmatic challenges are considered important. In our opinion, the first challenge of this study will be obtaining sufficient patients for inclusion in the study. Our study sample consists of complex and vulnerable patients with problems in multiple areas of life. Many of them have long mental health care histories and extensive criminal records. Former negative experiences with care or criminal justice services may have affected their attitude towards formal care and affiliated scientific research projects. Therefore, an additional social network intervention may not yet be indicated by care professionals during TAU or difficult to implement. Moreover, the majority of patients are obligated to participate in forensic treatment. Patient’s motivation for participation in a prolonged scientific research project and an additional intervention might therefore be low. Subsequently, the execution of a long follow-up period with multiple assessments in everyday clinical practice is expected to be challenging. In order to address these issues in inclusion and data collection, researchers will collaborate with mental health care professionals as much as possible considering the ethical and privacy guidelines. The researchers will participate in general team meetings. The team of researchers will be trained to keep an assertive, outreaching and flexible attitude towards both professionals and patients. Current contact information of the patient and his/her social network members is gathered actively during all follow-up assessments. Patients receive an appropriate financial compensation to emphasize our appreciation for their contribution and time-investment. Besides, researchers will put effort in building and maintaining contact with patients through phone and e-mail. When researches fail to reconnect with patients, network members will be contacted and home visits will be planned. A final important concern is the risk of nonadherence to intervention and treatment drop-out. To account for this risk, postponing the moment of randomization was considered. Unfortunately, the characteristics of the social network intervention do not allow this adjustment since the referral process (i.e. selection, intake and matching) of the intervention is complicated and time-consuming. Circumstances of patients might change during the referral period, therefore randomization must be performed as soon as possible after inclusion. Close cooperation with informal care will be used to enlarge the accessibility and attractiveness of the social network intervention. During the course of the study, at follow-up assessments, patients will be actively encouraged to participate in the intervention by researchers. Besides, when patients tend to drop-out professionals will be asked to motivate patients. Patients who drop-out during the study will still be included in the follow-up measures which enables us to examine profiles of treatment success and failure.

Finally, several methodological limitations should be considered. In order to promote generalizability of data and to examine which patients might benefit from the intervention, researchers chose to make the study accessible for a wide range of forensic patients. Consequently, this leads to a heterogeneous study sample which makes it difficult to achieve high internal validity. Furthermore, many changes in important areas of life, such as hospitalisations, relapses in substance (ab) use or criminal behaviour and changes in work, living environments and close relationships are expected to occur regularly during the study. These changes might influence the intervention and outcome measures. To account for these confounding factors, multiple participant and intervention characteristics will be recorded throughout the course of the study. Besides, the RCT design enables controlling for confounding factors between groups.

